**Fig. 2 Fig2:**
[figure not shown]
Statistical analysis with intention-to-treat principle. All recruited ELAIN patients randomly allocated to the early or late group will be considered for intention-to-treat. Patients with protocol violation will be included in the analysis to gain a representative result of the daily practice. Protocol violation is defined as: subjects in the early group who did not receive RRT in the early phase of AKI (KDIGO stage 2); and subjects in the late group who did not receive RRT, although KDIGO stage 3 was achieved and patients were lost to follow-up

Beyond the above primary analysis, the following pre-specified sensitivity analyses will be performed (see Fig. 2). In per-protocol analyses only patients without major protocol violations are included (see Fig. 3); in particular, patients are included only if they complete 90-day follow-up (complete case analysis). Using these data two kinds of analysis are performed in order to address two different questions.

**Fig. 3 Fig3:**
[figure not shown]
Statistical analysis with per-protocol principle. Patients with protocol violation will be excluded in the analysis to analyze the effect of both treatment arms. Protocol violation is defined as: subjects in the early group who did not receive RRT in the early phase of AKI (KDIGO stage 2); and subjects in the late group who did not receive RRT, although KDIGO stage 3 was achieved

In a first approach, the primary outcome is evaluated (overall survival in a 90-day follow-up period) using a two-sided inverse normal log-rank test [21]. The only difference to the primary analysis is that a per-protocol approach is pursued instead of an intention-to-treat analysis.In a second approach, data are reduced from the original primary outcome to the binary outcome ‘90-day mortality from all causes’. The binary outcome is created in order to provide comparability to other published study results. It is evaluated using a two-sided Chi-squared test.

Further statistical analyses of the primary outcome will be performed in order to address the fact that study patients have different risk profiles at the time of RRT initiation. The efficacy of the experimental and the control treatment may differ depending on the patient’s risk profile. For example ‘high risk’ patients may benefit from experimental treatment with early initiation of RRT substantially compared to control treatment, whereas in ‘low risk’ patients the ‘late’ approach may be superior. In order to address these questions, multivariable statistical analyses will be performed using Cox regression. Overall survival is modelled as a function of baseline risk (determined by pre-randomization baseline data such as the patient’s age, Acute Physiology and Chronic Health Evaluation (APACHE) score and SOFA score, as well as the baseline medical condition, i.e. severe sepsis/use of catecholamines/refractory fluid overload/development or progression of non-renal organ dysfunction), RRT treatment and the interaction of baseline risk and RRT treatment. In three different model approaches, RRT treatment is expressed in terms of: i) a time-dependent covariate that impacts survival starting with the time of RRT initiation; ii) the randomized treatment group; and iii) the time to initiation of RRT.

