### Inclusion criteria

All patients are eligible if they fulfill all inclusion criteria and no exclusion criteria. The inclusion criteria are as follows:Kidney Disease: Improving Global Outcomes (KDIGO) stage 2 (two-fold increase in serum creatinine from baseline and/or urinary output <0.5 ml/kg/h ≥12 h) (Table 1) despite optimal resuscitation: a) optimizing intravascular volume (fluid resuscitation: pulmonary artery occlusion pressure/central venous pressure of >12 mmHg, stroke volume variation <12 % in ventilated patients); b) optimization of cardiac index (>2.6 l/min per square meter); c) hemodynamic optimization (mean arterial pressure >65 mmHg); and d) normalizing intra-abdominal pressure (<15 mmHg);

**Table 1 Tab1:** Staging of acute kidney injury using KDIGO recommendations

Stage	Serum creatinine criteria	Urinary output criteria
1	Serum creatinine x 1.5 or serum creatinine rise of 0.3 mg/dl in 48 h	<0.5 ml/kg/h for 6 h
2	Serum creatinine x 2	<0.5 ml/kg/h for 12 h
3	Serum creatinine x 3 or serum creatinine ≥4 mg/dl or renal replacement therapy	<0.3 ml/kg/h for 24 h or anuria for 12 h

KDIGO, Kidney Disease: Improving Global Outcomes [6]Plasma neutrophil gelatinase-associated lipocalin (NGAL) >150 ng/ml;At least one of the following conditions: a) severe sepsis; b) use of catecholamines (norepinephrine or epinephrine >0.1 μg/kg/min); c) refractory fluid overload (worsening pulmonary edema, PaO2/FiO2 < 300 mmHg and/or fluid balance >10 % of body weight); and d) development or progression of non-renal organ dysfunction (Sequential Organ Failure Assessment (SOFA) score ≥2);Age between 18 and 90 years; andIntention to provide full intensive care treatment for at least 3 days.

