Nevertheless, the ELAIN trial has some limitations. The power calculation is based on data published a long time ago. Although the mortality of dialysis-dependent AKI decreased over the last 20 years [37], the mortality is still unacceptably high. A recently published meta-analysis regarding the initiation of renal replacement therapy analyzed 15 trials published between 1985 and 2011 and the authors showed that the overall 28-day mortality across the 15 trials was 55 % [13]. Although this study included older studies, a recently published trial investigating critically ill patients with a dialysis-dependent AKI also demonstrated that the 60-day all-cause mortality in critically ill patients with a dialysis-dependent AKI is 52 % [38]. Another limitation of the study is that we include critically ill patients with AKI stratified by hemodynamic SOFA score and urinary output accepting heterogeneity due to the inclusion of septic and non-septic patients. The pathophysiology of septic AKI is unique resulting in differences in clinical outcomes and responses to renal replacement therapy compared to non-septic patients [31]. But implementing a specific protocol with homogenous criteria for the diagnosis of critical illness and acute kidney injury combined with biomarkers is the first step to filling an important knowledge gap. Another limitation of such a trial design is that the investigators cannot be blinded and consequently there is a risk of contamination or unequal prescription of co-interventions. However, we adequately take this into account by a clear monitoring of all interventions.

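### The per-protocol set is not the set of patients who followed their assigned strategy: late-arm crossovers stay in, early-arm deaths and recoveries before RRT drop out, and losses are removed instead of censored

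*Protocol article*

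**What the plan says.** Primary outcome analyses builds the sensitivity set in two steps. First, "In per-protocol analyses only patients without major protocol violations are included (see Fig. 3". The Fig. 3 caption then defines a violation by two items: for the early arm, "subjects in the early group who did not receive RRT in the early phase of AKI (KDIGO stage 2"), and for the late arm, "subjects in the late group who did not receive RRT, although KDIGO stage 3 was achieved". Second, "patients are included only if they complete 90-day follow-up (complete case analysis"). Two analyses use this set: the inverse normal log-rank test on 90-day survival and a chi-squared test on binary 90-day mortality. Of the log-rank version the article says: "The only difference to the primary analysis is that a per-protocol approach is pursued instead of an intention-to-treat analysis". The caption gives the purpose of the exclusions as analysing the effect of the two treatment arms.

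The strategies themselves are set out in Treatment arms and Fig. 1. Early RRT starts at KDIGO stage 2 within 8 hours. Late RRT starts only at stage 3, within 12 hours of reaching it, or when a listed absolute indication is present. Fig. 1 adds that late-arm patients who never reach stage 3 remain in the late group for analysis. The Discussion concedes that, because investigators are not blinded, "there is a risk of contamination or unequal prescription of co-interventions".

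**The concern.** A per-protocol analysis should keep the patients who followed the strategy they were assigned. This one departs from that in three ways.

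1. **Crossovers.** A late-arm start before stage 3 without an absolute indication is the contamination that the Discussion fears, yet it matches neither listed violation. Table 1 adds to this, because it counts RRT itself as a stage 3 criterion: "Serum creatinine x 3 or serum creatinine ≥4 mg/dl or renal replacement therapy". A patient started too soon could thus be read as having reached stage 3. The 8-hour and 12-hour limits are not in the violation list either.
2. **Unequal treatment of early events.** Read literally, an early-arm patient who dies or recovers before RRT counts as untreated and is dropped. A late-arm patient who dies or recovers before stage 3 is kept.
3. **Losses.** Patients without complete 90-day follow-up are removed, although a log-rank test would use their time at risk. This is also a second difference from the primary analysis, where the text speaks of only one.

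At stake is how far the sensitivity analysis can support or question the primary result.

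**Working it through.** **Plan's own figures (Power and sample size; Interim analysis).** Inputs: 90-day mortality 55% late and 37% early, power 80%, two-sided alpha 0.05, O'Brien-Fleming with one interim analysis, 10% loss.
- HR = ln(0.63)/ln(0.45) = 0.579.
- Schoenfeld deaths, fixed design: 4 × (1.960 + 0.842)² / (ln 0.579)² = 104.9. With the two-look inflation of 1.0078 this is 105.7, so 106.
- 106/0.46 = 230; 230/0.90 = 255.6, so 256. The local levels 0.0052 and 0.0480 also reproduce.

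The design figures are sound, and nothing below changes them.

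**(1) Retained crossovers.** The article gives no crossover rate, so the share x is an assumption, as is early-arm mortality for those who cross. Late mortality = 0.55 − 0.18x; difference = 0.18 × (1 − x). Log-rank power is taken at 115 per arm, which is optimistic because the per-protocol set would be smaller.

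| x | late mortality | difference (points) | log-rank power |
|---|---|---|---|
| 0 | 55.0% | 18.0 | 80% |
| 10% | 53.2% | 16.2 | 71% |
| 20% | 51.4% | 14.4 | 61% |
| 30% | 49.6% | 12.6 | 50% |

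Intention-to-treat carries the same dilution by design. A per-protocol analysis is meant to remove it, and this one does not.

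**(2) Deaths and recoveries before RRT.** At constant hazard, the share dying within 8 hours is about −ln(1 − p)/90 × 8/24.
- p = 0.37: 0.4620/270 = 0.17%.
- p = 0.55: 0.7985/270 = 0.30%.

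So about 0.2 to 0.3% of the arm, and more if the hazard in the first hours exceeds the average. Suppose there is no true effect and mortality is 46% in both arms. Dropping a share d of early-arm deaths gives (0.46 − d)/(1 − d):
- d = 0.3%: 0.457/0.997 = 45.8%, a spurious benefit of about 0.2 points.
- d = 2% (assumed): 44.9%, 1.1 points; chi-squared rejection rate 5.3%.
- d = 5% (assumed): 43.2%, 2.8 points; rejection rate 7.1%.

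Two other exclusions push the opposite way.
- Early-arm patients who recover before RRT are also dropped. If 2% do so and all survive (assumed), early mortality reads 0.46/0.98 = 46.9%, which is 0.9 points against early RRT.
- Late-arm patients who reach stage 3 and die before RRT are dropped too. At 55% mortality and constant hazard, the 12-hour window gives 0.7985/180 = 0.44% of those who reach stage 3.

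**(3) Complete cases.** Assume exponential death and loss times. Death hazard a = −ln(1 − p)/90; loss hazard b is chosen so that the stated share is lost before death and before day 90. The complete-case rate is dead/(dead + known alive).
- 10% lost in each arm: 0.3483/0.90 = 38.7% and 0.5147/0.90 = 57.2%. The difference is 18.5 points instead of 18.
- No true effect, 46% in both arms: equal loss gives no difference. Loss of 5% early and 15% late gives 47.0% against 49.1%, a false difference of 2.1 points (rejection rate 6.2%).

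**(4) Stage 3 wording.** Table 1 accepts creatinine of at least 4 mg/dl alone; Treatment arms also asks for an acute rise of at least 0.5 mg/dl within 48 hours. A late-arm patient managed by the second and never given RRT can be labelled a violator under the first. Anuria, a stage 3 item in Table 1, appears in Treatment arms as an absolute indication, so it triggers RRT under both.

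**The case against.** Only the intention-to-treat analysis is confirmatory, trial investigators themselves start RRT, and daily visits check adherence, so crossover may be rare. The article openly labels the set a complete case analysis. It also plans Cox models with RRT as a time-dependent covariate and with time to initiation, so actual timing is not left unexamined. The word major, or the full protocol, might grade violations further. All of this limits the weight of the point. It does not repair the caption, which gives an explicit definition to which the body text refers. The Cox models answer a different question from a per-protocol comparison.

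Three stronger readings are tempting, and the document does not support them.
- A reader might infer that the exclusions favour early RRT. Dropped early-arm deaths do, but dropped recoveries and dropped late-arm deaths after stage 3 work the other way, and the article gives no figures with which to weigh them.
- A reader might take a large complete-case distortion by assuming that every lost patient survived: 0.37/0.90 = 41.1% and 0.55/0.90 = 61.1%. That is an extreme assumption; ordinary loss gives 38.7% and 57.2%.
- A reader might infer that binary 90-day mortality is examined only in this set. Outcomes and Primary outcome analyses also plan 90-day mortality rates by randomised group, though only if the survival difference is significant. The abstract lists 90-day mortality as a secondary endpoint, and chi-squared tests are planned for binary secondary data.

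**Conclusion.** The point holds as a minor to moderate one. Followed as written, the per-protocol set keeps late-arm crossovers and so dilutes the contrast it is meant to isolate, by 1.8 points for each 10% of the late arm that crosses over with early-arm mortality; the rate itself is an assumption. The unequal handling of deaths and recoveries before RRT is an inference from literal wording, since the text does not mention them. Its net direction cannot be determined, and the part due to deaths in the 8-hour window is probably small. Removing losses is needless for the log-rank test and biases the comparison mainly if loss is informative or differs between arms. The creatinine mismatch touches a narrow group. The primary test, alpha, 106 deaths, 230 evaluable and 256 recruited patients stand.

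**What to change.** Amend the per-protocol definition before outcomes by arm are seen:
- Define violations symmetrically against each arm's assigned strategy. Add late-arm RRT started before the Treatment arms criteria are met without a listed absolute indication, and starts outside the stated 8-hour and 12-hour windows.
- In neither arm count a patient who dies before the initiation window closes as a violator, and state how recovery before RRT is classified.
- In the per-protocol log-rank analysis, censor lost patients at last contact. Align the captions of Figs. 2 and 3, of which only the first mentions loss to follow-up.
- Also report the binary 90-day comparison on all randomised patients, whether or not the primary test is significant.
- Reconcile the creatinine wording of stage 3 in Table 1 and Treatment arms before anyone is classified.

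The cost is wording. RRT start times are already needed for the planned Cox models. The article does not say whether the reason for starting RRT is recorded; if it is not, the trigger would have to be derived from the documented renal and laboratory data. The added violations make the per-protocol set somewhat smaller.

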### Treatment arms

Early initiation of RRT will be initiated at stage 2 of the KDIGO classification within 8 hours:Urine output <0.5 ml/kg/h for ≥12 h; and/orTwo-fold increase of the serum creatinine level compared to the baseline value.

Late initiation of RRT will be initiated when stage 3 of the KDIGO classification (not later than 12 hours after achieving stage 3) is achieved:Urine output <0.3 ml/kg/h for ≥24 h; and/or > Three-fold increase of the serum creatinine level compared to the baseline value; and/orSerum creatinine of ≥4 mg/dl with an acute increase of at least 0.5 mg/dl within 48 hours.

Or if any of the following absolute indications for RRT are present:Urea serum levels >100 mg/dl;Potassium serum levels >6 mmol/l and/or ECG abnormalities;Magnesium serum levels >4 mmol/l;Urine production <200 ml/12 h or anuria (without diuretics, according to the KDIGO recommendations); andOrgan edema in the presence of AKI resistant to diuretic treatment (one attempt with loop diuretics prior to randomization).

After enrolment, ELAIN investigators are responsible for the catheter insertion and the initiation of RRT (see Additional file 1). Daily visits will be performed to ensure adherence to the protocol. Hemodynamic, pulmonary, inflammation, renal and laboratory data will be documented. Education to ensure proper implementation of the study protocol was done prior to starting enrolment. Project manager and trial investigators conduct monthly conferences to monitor all aspects of the protocol.

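### The late-arm per-protocol violation rule names only KDIGO stage 3, so a never-treated late patient with only an absolute indication for RRT counts as adherent

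*Protocol article*

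**What the plan says.** Treatment arms gives the late group two routes to RRT. The first is a stage 3 list: urine output below 0.3 ml/kg/h for at least 24 h, creatinine more than three-fold above baseline, or creatinine of at least 4 mg/dl "with an acute increase of at least 0.5 mg/dl within 48 hours". The second is introduced by "Or if any of the following absolute indications for RRT are present" and lists urea, potassium and/or ECG abnormalities, magnesium, low urine output and diuretic-resistant organ edema. The urine item reads "Urine production <200 ml/12 h or anuria". The Fig. 1 caption also names stage 3 and absolute indications as separate triggers.

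The Fig. 3 caption defines the violations that lead to exclusion from the per-protocol analysis. For the late arm it lists "subjects in the late group who did not receive RRT, although KDIGO stage 3 was achieved" and nothing else. The consequence is explicit: "Patients with protocol violation will be excluded in the analysis to analyze the effect of both treatment arms". The Fig. 2 caption, on the intention-to-treat analysis, uses the same stage-3-only wording for the late arm.

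Two analyses use the per-protocol set: the inverse normal log-rank test on 90-day survival and a Chi-squared test on binary 90-day mortality. Of the log-rank analysis the protocol says: "The only difference to the primary analysis is that a per-protocol approach is pursued instead of an intention-to-treat analysis".

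**The concern.** A per-protocol set should keep patients who were managed as the protocol required and remove those who were not. Here the rule that requires treatment has two triggers, while the rule that identifies non-treatment as a violation has one. A late patient who met only the missing trigger and never received RRT would be labelled adherent.

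The error is confined to the late arm and depends on the clinical course after randomization. The per-protocol log-rank test is meant to differ from the primary analysis only through the choice of patients, so the violation definition largely determines what it adds. At stake is how far the two sensitivity analyses show the effect of the strategies as delivered.

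**Working it through.** The point has no planned figure of its own, so the check is whether the two rules cover the same patients.

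**Step 1: compare the triggers.** For each absolute indication in Treatment arms, is it also a stage 3 criterion in that section's own list, or in Table 1 (Inclusion criteria)? Table 1 gives stage 3 as "Serum creatinine x 3 or serum creatinine ≥4 mg/dl or renal replacement therapy" for creatinine and "<0.3 ml/kg/h for 24 h or anuria for 12 h" for urine output.

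| Absolute indication | In the Treatment arms stage 3 list | In Table 1 stage 3 |
|---|---|---|
| Urea >100 mg/dl | no | no |
| Potassium >6 mmol/l and/or ECG abnormalities | no | no |
| Magnesium >4 mmol/l | no | no |
| Urine <200 ml in 12 h | no | no |
| Anuria | not named | yes, if for 12 h |
| Diuretic-resistant organ edema | no | no |

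Only anuria overlaps, and only with Table 1. Table 1 also counts RRT itself as stage 3, but a never-treated patient cannot reach stage 3 that way.

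**Step 2: the urine item.** It is a 12-hour volume, while stage 3 needs a weight-based rate over 24 hours. At assumed body weights, 200 ml in 12 h is:
- 50 kg: 200/12/50 = 0.33 ml/kg/h
- 70 kg: 200/12/70 = 0.24 ml/kg/h
- 100 kg: 200/12/100 = 0.17 ml/kg/h

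In a light patient even the rate need not fall below 0.3. In a heavier patient it does, but for 12 h rather than 24 h.

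**Step 3: two constructed late patients, neither ever treated.**
- Creatinine rises from 1.0 to 2.5 mg/dl (2.5/1.0 = 2.5-fold, below 4 mg/dl), urine is 0.4 ml/kg/h and urea is 110 mg/dl. Stage 3 is not reached, but RRT was required because of urea.
- An 80 kg patient without diuretics passes 190 ml in 12 h (190/12/80 = 0.20 ml/kg/h), then 600 ml in the next 12 h. The 24 h mean is (190 + 600)/24/80 = 0.41 ml/kg/h. With creatinine below its stage 3 limits, stage 3 is not reached, but RRT was required because of the 12 h volume.

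Both stay in the per-protocol set under the Fig. 3 rule, whichever stage 3 definition is used.

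**Step 4: illustrative size.** Power and sample size gives 106/0.46 = 230 patients in the final analysis and 230/0.90 = 255.6, so 256 recruited. Both figures reproduce, and neither uses the per-protocol rule. With 1:1 allocation the late arm has 230/2 = 115 patients. At the planned 55 % mortality that is 0.55 × 115 ≈ 63 deaths, or 63/115 = 54.8 %. The number wrongly kept is not in the article. I assume 1 to 5, with every other late patient in the per-protocol set, and remove them:

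| Removed | All had died | All had survived |
|---|---|---|
| 1 | 62/114 = 54.4 % (−0.4 points) | 63/114 = 55.3 % (+0.5 points) |
| 5 | 58/110 = 52.7 % (−2.1 points) | 63/110 = 57.3 % (+2.5 points) |

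The planned difference is 55 − 37 = 18 points.

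**The case against.** The strongest reply is that a figure caption in a condensed article is shorthand. The running text of Primary outcome analyses excludes only major violations, and a full list may sit elsewhere. The caption is also silent on the 8 h and 12 h start limits, which suggests that it was not meant to be exhaustive. However, the caption presents its content as the definition, the running text points to Fig. 3 for it, and the only addition made there is completion of 90-day follow-up. This is a stated rule that conflicts with the start rule, rather than detail left for later.

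A sponsor could also hold that a brief absolute indication, such as a raised potassium corrected medically, is not a major violation. That is defensible, but the article does not say it. As written, all absolute indications are left out, lasting ones included.

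The practical reach is limited, and this part of the reply stands. A patient matters only if an absolute indication occurred, stage 3 never did, RRT was never given, and 90-day follow-up was complete. The trial's investigators are responsible for starting RRT and make daily visits to check adherence.

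A reader might infer a second error in the opposite direction: Table 1 counts creatinine of at least 4 mg/dl without the recent rise that Treatment arms demands, so some late patients could be excluded although no RRT was due. The document does not support this as a finding. Treatment arms spells out what stage 3 means for late initiation, and that is the natural reading in a rule about late initiation. The case would need a baseline creatinine of at least 4/3 = 1.33 mg/dl, and it nearly vanishes if the rise may fall in any 48 h window.

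**Conclusion.** The concern holds as a minor inconsistency. Followed as written, the Fig. 3 rule keeps never-treated late patients who had an absolute indication but not stage 3, although Treatment arms required RRT for them. The textual mismatch is certain; its practical effect is not. The count cannot be derived and is probably small. The 1 to 5 patients used above are an assumption without a source, and the outer limits of about 2 points either way require all five to have died or all five to have survived.

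A reader might go on to infer a bias in a known direction, or a threat to the main result. Neither follows. The direction depends on the outcomes of patients whom the article does not describe. The confirmatory analysis is by intention to treat and includes violators, so the primary test, alpha, power and sample size do not change. Bedside decisions to start RRT follow Treatment arms and do not change either.

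**What to change.** In the Fig. 3 caption, define the late-arm violation as no RRT given although at least one late-start criterion in Treatment arms was met, that is, an item of its stage 3 list or an absolute indication. Use the same wording in the Fig. 2 caption so that the term has one meaning throughout; this does not alter the intention-to-treat set. If the sponsor wants brief, medically corrected indications not to count as major, the definition should say so.

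Make the change by written amendment, the route the protocol already provides under Interim analysis. Because investigators are not blinded and recruitment is active, settle it before outcomes are compared by arm.

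The cost is small. A few untreated late patients leave the per-protocol set, and late patients already enrolled must be checked once against recorded laboratory and urine data.

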**Methods/design:**

Our plan is to randomize critically ill patients with acute kidney injury to ‘early’ or ‘late’ initiation of renal replacement therapy according to stage 2 and 3 of the KDIGO classification using a specific trial protocol. We plan to guide data collection and analysis using pre-existing definitions and testing. The primary endpoint is overall survival in a 90-day follow-up period. Secondary endpoints include 28-day, 60-day, 90-day and 1-year all-cause mortality, recovery of renal function, ICU and hospital length-of-stay. The primary analysis will be an intention-to-treat analysis; secondary analyses include treated analyses. We will also specify rules for handling data and determining outcome.

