### Power and sample size

Power calculations are performed based on the primary endpoint, i.e. the overall survival in a 90-day follow-up period. The primary efficacy analysis is intended to test whether early versus late initiation of RRT in intensive care patients with AKI results in different overall survival in a 90-day follow-up period.

An adaptive design based on a group sequential plan according to O’Brien and Fleming with one interim analysis and a global (two-sided) significance level α = 0.05 is applied (see below). The expected 90-day mortality rate in the control group with late initiation of RRT is 55 % (based on literature research [7–10, 20–24]). Differences between treatment groups are to be detected with a power of 80 %, if the 90-day mortality rate in the experimental intervention group with early initiation of RRT is 37 % or smaller. The expected treatment effect of 18 % is calculated on the mortality differences between the early and late groups resulting from the studies of our literature research [7–10, 20–24] (see Additional file 3). The interim analysis is conducted at the time when half of the total number of deaths has been observed (information rate 0.5). Follow-up of each patient will be 90 days. Resulting from these considerations, the interim analysis is performed after 53 deaths have been observed across both treatment groups. The final analysis is planned to be performed after 106 deaths have been observed in total across both treatment groups, i.e. assuming an average of 46 % mortality rate in the 90-day follow-up period, a total number of 106/0.46 = 230 patients across both treatment groups is included in the final analysis. This corresponds to 256 recruited patients, if an expected number of 10 % of recruited patients is assumed to be lost to follow-up and in the worst case has completely non-evaluable data. Power calculations are to be performed based on a two-sided inverse normal log-rank test [25], using ADDPLAN software (ICON, Dublin, Ireland).

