### Interim analysis

A group sequential plan according to O’Brien and Fleming with one interim analysis is established. In order to maintain a global significance level alpha = 0.05, the interim and the final analysis are performed on local significance levels of 0.0052 and 0.0480, respectively. Based on the group sequential plan, an adaptive design is applied, that admits two possible design changes after the interim analysis: i) the number of deaths of the final analysis will be re-calculated applying the inverse normal method [26]; and ii) the schedule and the number of further interim analyses may be modified applying the conditional rejection error probability (CREP) principle [27, 28].

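### The only explicit test of binary 90-day mortality, and both labelled sensitivity analyses, use per-protocol completers; intention-to-treat 90-day rates are promised only after a significant log-rank test

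*Protocol article*

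**What the plan says.** All places are in the Protocol article.

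- **Primary outcome analyses.** The confirmatory analysis is a two-sided inverse normal log-rank test of survival over 90 days in all randomised patients, by intention to treat. The 90-day all-cause mortality rate in each group is then estimated, on condition that the survival difference is significant. The Outcomes section repeats that condition.
- **Primary outcome analyses, text after the Fig. 2 caption.** The pre-specified sensitivity analyses are per-protocol, and "patients are included only if they complete 90-day follow-up (complete case analysis). Using these data two kinds of analysis are performed".
- **Primary outcome analyses, text after the Fig. 3 caption.** The first of the two repeats the log-rank test, and the per-protocol approach is described as its sole departure from the primary analysis. The second is the Chi-squared test of binary 90-day mortality, with the reason given that "The binary outcome is created in order to provide comparability to other published study results". Cox models of overall survival follow, and one of them uses the randomised group.
- **Abstract, Methods/design.** "Secondary endpoints include 28-day, 60-day, 90-day and 1-year all-cause mortality". The Outcomes section lists 28-day, 60-day and 1-year overall survival as secondary, and no 90-day item.
- **Secondary and tertiary outcome analyses.** Binary data are compared by Chi-squared, with no analysis population named.
- **Power and sample size.** A tenth of "recruited patients is assumed to be lost to follow-up and in the worst case has completely non-evaluable data". This allowance is used to raise 230 patients to 256.

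**The concern.** There are three linked problems, all in what the text states.

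1. **Analysis set.** The one explicit test of binary 90-day mortality excludes protocol violators and anyone without complete follow-up. Both exclusions happen after randomisation and can depend on treatment and prognosis. Comparability with published results does not require either.
2. **Condition on significance.** The all-randomised 90-day rates depend on a significant log-rank test. A neutral trial is where readers most need an unselected absolute difference with its uncertainty. There, the only explicit rate comparison left is the selected one.
3. **Two changes at once.** The per-protocol log-rank test is presented as differing from the primary analysis in one respect, yet the completer rule also removes lost patients. The binary test changes the outcome as well. If either disagrees with the primary result, the reader cannot tell whether adherence or loss is responsible. The figure captions add to this: Fig. 2 appears to count loss to follow-up among the protocol violations, and Fig. 3 does not.

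At stake is how the trial's absolute mortality effect is reported and how robust it can be shown to be. Control of the type I error is not at stake.

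**Working it through.** **Inputs (Power and sample size; Interim analysis).** A plan "with one interim analysis and a global (two-sided) significance level α = 0.05 is applied"; analyses "performed on local significance levels of 0.0052 and 0.0480, respectively"; "The expected 90-day mortality rate in the control group with late initiation of RRT is 55" per cent; the trial is sized "with a power of 80 %, if the 90-day mortality rate in the experimental intervention group with early initiation of RRT is 37 % or smaller". Allocation is 1:1 (Enrolment), the interim information rate is 0.5, and assumed loss is 10%.

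**Step 1: reproduce the plan's figures.**
- Hazard ratio = ln(1 − 0.37)/ln(1 − 0.55) = 0.579.
- Schoenfeld events, fixed design = 4(1.960 + 0.842)²/(ln 0.579)² = 104.9.
- Two-stage O'Brien-Fleming inflation, found numerically, is 1.0078: 104.9 × 1.0078 = 105.7, so 106 deaths. The local levels recompute to 0.0052 and 0.0480.
- 106/0.46 = 230.4, so 230 evaluable; 230/0.90 = 255.6, so 256 recruited.

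The sample size is sound and gives a fair base for illustration.

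**Step 2: compare the planned loss with the planned effect.** 256 − 230 = 26 patients lost. Among 115 completers per arm, expected deaths are 0.55 × 115 ≈ 63 (late) and 0.37 × 115 ≈ 43 (early), an excess of 20. The planned loss is therefore larger than the planned excess of deaths.

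**Step 3: what a completer analysis cannot show.** Assume 13 lost per arm; equal loss is an assumption. P values are from the uncorrected Chi-squared test.

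| Outcome of lost patients | Late | Early | Difference | p |
|---|---|---|---|---|
| Excluded (completers) | 63/115 = 54.8% | 43/115 = 37.4% | 17.4 points | 0.008 |
| All lost alive | 63/128 = 49.2% | 43/128 = 33.6% | 15.6 points | 0.011 |
| All lost dead | 76/128 = 59.4% | 56/128 = 43.8% | 15.6 points | 0.012 |
| Early lost all die, late lost none | 63/128 = 49.2% | 56/128 = 43.8% | 5.5 points | 0.38 |
| Late lost all die, early lost none | 76/128 = 59.4% | 43/128 = 33.6% | 25.8 points | <0.0001 |

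The middle ground is less dramatic. If 7 of the 13 late losses die, p is 0.045 with 11 of 13 early losses dead and 0.061 with 12 of 13.

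**Step 4: a milder selection.** Suppose true mortality is 37% and 55% and the 10% loss falls only on day-90 survivors. Completer mortality is then 0.37/0.90 = 41.1% and 0.55/0.90 = 61.1%, a difference of 20.0 points against a true 18.

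**Step 5: power of the binary test (55% vs 37%, two-sided 0.05).** It is 82.8% with 128 per arm of known status and 78.6% with 115 per arm. If per-protocol exclusions remove a further 5%, 10% or 20% of completers (an assumed range, not in the protocol), it is 76.4%, 74.0% or 69.1%.

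**The case against.** The strongest reply is that the main question is already answered by intention to treat. A reader might infer from the completer restriction that 90-day mortality is never tested in the randomised groups. The text does not support that: the confirmatory log-rank test compares all-cause death through day 90 in everyone randomised, and after a significant result the rates in both groups follow. This stands, and it confines the point to the binary comparison and to the case of a non-significant result.

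A reader might also infer that every supporting analysis is per-protocol. Only the two labelled as sensitivity analyses are; the Cox models are not stated to be limited to completers.

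The Abstract's secondary list, read with the general Chi-squared rule for binary data, could be taken to supply an unrestricted test of 90-day mortality. That is possible but weak. The Outcomes list has no 90-day secondary item, perhaps because day 90 is already primary, and it words its mortality items as overall survival, which the analysis section assigns to the log-rank test.

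Detailed missing-data rules may sit in the full protocol or analysis plan, and the Abstract says that data-handling rules will be specified. It therefore cannot be said that the effect of loss is never examined. What can be said is that the sensitivity analyses described here do not isolate it.

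Finally, the studies in the Background are described as limited to patients who received RRT, so intention-to-treat proportions would not match them exactly either. That is fair, but it gives no reason to drop patients for incomplete follow-up.

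**Conclusion.** The point holds in a limited form. The only explicit test of binary 90-day mortality and both labelled sensitivity analyses are placed in per-protocol completers. All-randomised 90-day rates are promised only after a significant log-rank test. The two sensitivity analyses mix adherence with loss, despite the statement that the first differs from the primary analysis in one respect. The confirmatory test, the sample size and the significance levels are unaffected.

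The range of 5.5 to 25.8 points rests on the planned 10% loss, equal loss per arm and completer mortality at plan values. Each end requires every lost patient in one arm to die and none in the other. A reader might take the lower end to mean that the trial's result is fragile. The documents do not support that: 10% is a planning allowance, and in the balanced scenarios the difference stays near 16 points. The range shows only what a completer analysis leaves out of sight.

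**What to change.** In Primary outcome analyses:

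1. Run the binary 90-day comparison in the full analysis set, for example as a Kaplan-Meier 90-day risk difference with 95% confidence interval, and report it whether or not the log-rank test is significant.
2. Keep both per-protocol analyses as supportive. State that they differ from the primary analysis in adherence and in follow-up, and align the Fig. 2 and Fig. 3 definitions of protocol violation on loss to follow-up.
3. Add one sensitivity analysis in all randomised patients that changes only the assumed outcome of those lost: all alive, all dead, and a tipping point by arm. This is needed alongside item 1, because a Kaplan-Meier estimate itself assumes non-informative censoring and does not test it.
4. Reconcile the Abstract's secondary endpoints with the Outcomes list on 90-day mortality.

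The cost is plan wording and a few extra tables on data already collected. The downside is that the reported mortality result may look less clean than the completer figure.
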